### Sample size calculation

As this is the first study on the efficacy of a mobile phone-based life-skills training for substance use prevention, we could not rely our calculations on conclusive results of similar studies. Instead, our calculations were based on the effect sizes of traditional face-to-face delivered life skills training programs in educational settings. However, to account for the longer duration and higher intensity of traditional life-skills trainings compared to our mobile phone-based training, these estimates based on the effect sizes of traditional face-to-face delivered life skills training programs were revised downwards, resulting in a more conservative estimation.

An estimation of the expectable effect sizes was based on the results of a Cochrane Review on school-based programmes for preventing smoking [7] and on the efficacy of a program for the prevention of binge drinking in adolescents based on the Life Skills Training [30]. The Cochrane Review revealed a statistically significant effect in preventing the onset of smoking for combined social competence and social influences curricula (six RCTs) with an Odds Ratio of 0.49 (95% CI 0.28–0.87). The program for the prevention of binge drinking in adolescence based on the Life Skills Training revealed an intervention effect on problem drinking at the 1-year follow-up, with an odds ratio (OR) of 0.41 (95% CI 0.18–0.93), and at the 2-year follow-up with an OR of 0.40 (95% CI 0.22–0.74). Based on these studies, and a slight downward correction, an OR of 0.60 was expected for the main outcome measures.

Based on an estimated OR of 0.60 and an expected 30-days-prevalence of problem drinking in 16 year-old adolescents of 25% in the control group at the 18-month follow-up (mean of prevalence in 15-year olds derived from HBSC study [5] and in 17-year olds derived from Addiction Monitoring [31]), a sample size of *n* = 370 in each study group would be required to have 80% power for a χ^2^-test (α = 5%, 2-sided) in order to detect this difference based on a calculation using G-Power.

Based on an estimated OR of 0.60 and an expected 30-days prevalence of tobacco smoking in 16 year-old adolescents of 22% in the control group at the 18-month follow-up (mean of prevalence in 15-year olds derived from HBSC study [5] and in 17-year olds derived from Addiction Monitoring [31]), a sample size of *n* = 410 in each study group would be required to have 80% power for a χ^2^-test (α = 5%, 2-sided) in order to detect this difference.

As secondary school students are nested within school classes, we additionally need to consider a potential design effect for the calculation of the sample size for our study. Based on [26, 32], an average cluster size of 13 study participants per school class and an intra-cluster correlation coefficient of 0.05 could be expected. This would result in a design effect of 1.60. Multiplying this design effect by the required size for an unnested sample (*n* = 410) results in a required sample size of *n* = 656 per study group and a total of *n* = 1312 study participants. Thus, based on the participation rates of the previous MobileCoach studies [32, 33] and the pre-post study on a mobile phone-based life- skills training, approximately 100 secondary school classes are required to reach this sample size.

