**Methods/design:**

The efficacy of a mobile phone-based life-skills training to prevent substance use among adolescents will be tested in comparison to an assessment only control group, within a cluster-randomised controlled trial with two follow-up assessments after 6 and 18 months. The fully automated program is based on social cognitive theory and addresses self-management skills, social skills, and substance use resistance skills. Participants of the intervention group will receive up to 4 weekly text messages over 6 months in order to stimulate (1) positive outcome expectations, e.g., on using self-management skills to cope with stress, (2) self-efficacy, e.g., to resist social pressure, (3) observational learning, e.g. of interpersonal competences, (4) facilitation, e.g., of strategies to cope with negative emotions, and (5) self-regulation, e.g., by self-monitoring of stress and emotions. Active program engagement will be stimulated by interactive features such as quiz questions, message- and picture-contests, and integration of a friendly competition with prizes in which program users collect credits with each interaction. Study participants will be 1312 students between the ages of 14 and 16 years from approximately 100 secondary school classes. Primary outcome criteria will be problem drinking according to the short form of the Alcohol Use Disorders Identification Test and cigarette smoking within the last 30 days preceding the follow-up assessment at month 18.

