Follow-up assessments after 6 and 18 months will be conducted by a research assistant, within the participating school classes, during regular school lessons and using tablet computers. Computer-assisted telephone interviews will be conducted by a research assistant when assessments cannot take place during a school lesson because of vacations, class resolution, or study participants’ absence from class.

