### Data analyses

Generalized Linear Mixed Models will be used to test intervention effects for binary outcomes and linear mixed models for continuous outcomes [43, 44]. These models account for both fixed and random effects and are particularly useful in analysing longitudinal and nested data (e.g., time within students, students within school classes). To test the efficacy of the intervention, we will test the variables “study group”, “time” and their interaction “study group x time” as predictors of the outcome criteria assessed at follow-up. If necessary, we will control for baseline differences by adding additional baseline variables as covariates to the models. We will conduct both (1) intention to treat analyses and (2) complete case analyses considering all study participants with available follow-up data. For ITT analyses, we will use multiple imputation procedures as described elsewhere [45].

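### The 1312 students needed with a month-18 outcome are also the 1312 to be enrolled, so the stated 80% power for smoking has no allowance for loss to follow-up

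*Protocol article*

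**What the plan says.** The Sample size calculation section of the protocol article gives the whole chain. For both primary outcomes, "an OR of 0.60 was expected for the main outcome measures". The control-group prevalences, 22% for smoking and 25% for problem drinking, are those expected at the 18-month follow-up. The unclustered requirement is 410 per arm for smoking and 370 for problem drinking; each is the number that "in each study group would be required to have 80% power for a" chi-square test ("α = 5%, 2-sided) in order to detect this difference").

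Clustering is then added with "an average cluster size of 13 study participants per school class" and an intra-cluster correlation of 0.05. This gives a design effect of 1.60, hence 656 per arm and 1312 in total. The section turns that total into classes through the participation rates of earlier studies: "approximately 100 secondary school classes are required to reach this sample size".

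The Abstract (Methods/design) uses the same total for enrolment: "Study participants will be 1312 students between the ages of 14 and 16 years from approximately 100 secondary school classes".

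Two other sections bear on follow-up. Participants, setting and procedure provides telephone interviews where an assessment cannot be held in class, for example "because of vacations, class resolution" or absence. Data analyses plans multiple imputation for the intention-to-treat analysis and, alongside it, "complete case analyses considering all study participants with available follow-up data".

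**The concern.** A sample size built on month-18 prevalences counts students who have a month-18 outcome. If that count is also the enrolment target, the 80% holds only if nobody is lost over 18 months. Participation rates do not help, because they describe uptake at baseline and not retention. Nor is a margin hidden in the class count: 1312 / 13 = 100.9 classes, so the 13 per class are enrolled students.

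Multiple imputation handles bias under its assumptions, but it does not by itself restore the information that missing outcomes would have carried.

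What is at stake is how a null result is read. Smoking is one of two primary outcomes and the one that fixed the sample size. A non-significant smoking result would be judged against 80% power for an odds ratio of 0.60, when the power on the protocol's own method would be lower by an amount that depends on retention.

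**Working it through.** **Inputs from the Sample size calculation section:** two-sided alpha 0.05; odds ratio 0.60; control prevalence 22% (smoking) and 25% (problem drinking); 13 students per class on average; ICC 0.05; 656 per arm.

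**Inputs assumed here:** the proportion lost by month 18, d, and the coefficient of variation (CV) of class size. The article gives neither, so a range is shown.

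**Step 1: reproduce the plan's figures.**
- Intervention prevalence from the odds ratio: odds 0.60 × 0.22/0.78 = 0.1692, so 14.47% for smoking; odds 0.60 × 0.25/0.75 = 0.20, so 16.67% for drinking.
- n per arm for two proportions at 80% power: smoking 413 (pooled variance) or 410 (unpooled), against 410 stated; drinking 372 or 369, against 370 stated. Both reproduce.
- Design effect: 1 + (13 − 1) × 0.05 = 1.60.
- 410 × 1.60 = 656 per arm; × 2 = 1312.
- Power at 410 effective per arm, pooled test: 79.8% for smoking. The same 410 gives 83.7% for drinking, which needs only 370.

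**Step 2: introduce loss, with equal classes.** Loss reduces the analysed students and also the analysed class size, which lowers the design effect:
- m = 13 × (1 − d)
- DEFF = 1 + (m − 1) × 0.05
- effective n per arm = 656 × (1 − d) / DEFF

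Example at d = 20%: m = 10.4; DEFF = 1 + 9.4 × 0.05 = 1.47; effective n = 524.8 / 1.47 = 357.

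| Loss (assumed) | DEFF | Effective n per arm | Power, smoking | Power, drinking |
|---|---|---|---|---|
| 0% | 1.600 | 410.0 | 79.8% | 83.7% |
| 5% | 1.567 | 397.6 | 78.6% | 82.6% |
| 10% | 1.535 | 384.6 | 77.2% | 81.3% |
| 15% | 1.502 | 371.1 | 75.8% | 79.9% |
| 20% | 1.470 | 357.0 | 74.1% | 78.4% |
| 30% | 1.405 | 326.8 | 70.3% | 74.8% |

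**Step 3: unequal class size, as a sensitivity figure only (smoking, no loss).** The article calls 13 an average, and the factor 1.60 is exact only if every class has 13. Two approximations bracket the effect.
- Equal weight per student: DEFF = 1 + [(1 + CV²) × 13 − 1] × 0.05. At CV 0.4 this is 1.704, effective n 385.0, power 77.3%. At CV 0.5 it is 1.763, effective n 372.2, power 75.9%.
- Mixed-model relative efficiency: 1 − CV² × λ(1 − λ), with λ = 13 × 0.05 / (13 × 0.05 + 0.95) = 0.406. At CV 0.4 this is 0.961, effective n 394.2, power 78.2%. At CV 0.5 it is 0.940, effective n 385.3, power 77.3%.

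So smoking power is about 77–78% at CV 0.4 and 76–77% at CV 0.5.

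**The case against.** The strongest objection is that the planned analysis is not a chi-square test. Data analyses specifies mixed models with study group, time and their interaction, and baseline covariates if necessary. Such a model may recover power that the unadjusted comparison loses. A reader might therefore infer from the table that the trial as analysed will miss 80%. The documents do not support that: the figures apply to the unadjusted test to which the protocol ties its 80%. They do not support the opposite either. A gain from baseline information depends on the baseline prevalence of 30-day smoking and its association with the month-18 outcome. The article gives neither, and it claims no such gain.

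A reader might also infer that both primary outcomes are underpowered. That is too strong. Problem drinking has a reserve and falls to about 80% only at about 15% loss with equal classes.

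The telephone interviews, and the 10 Swiss Francs offered for each follow-up, are measures to keep students in the study, not forecasts of loss. This is fair. The article states no expected loss rate, and at 5% loss smoking power is only about one point below its starting value. What remains is that missing follow-up data are provided for in the analysis and not in the sample size.

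Using the average class size is ordinary practice, and the simpler unequal-size formula is conservative for a mixed model. For that reason the class-size point is kept as a sensitivity figure.

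Finally, an article condenses a fuller protocol. Here, however, every step from the odds ratio to the number of classes is printed, and the chain ends at enrolment without a step for loss.

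**Conclusion.** The point holds as a planning omission, not as an arithmetic error. The stated 80% for smoking, on the stated chi-square test, requires a month-18 outcome from every enrolled student. Any loss takes it below that. The direction is certain. The size rests on assumed loss, with equal classes and the protocol's own odds ratio, prevalences and ICC: roughly one point at 5%, under three at 10%, under six at 20% and over nine at 30%, measured from 79.8%. For problem drinking the stated 80% is kept to about 15% loss, under the same assumptions.

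**What to change.** Keep the enrolment target of 1312. In the Sample size calculation section:
- State the retention assumed at month 18, with its basis and a plausible range.
- Restate the power for each primary outcome at the number expected with month-18 data, allowing for the smaller analysed class size.
- Say that these figures refer to the unadjusted comparison.
- Give unequal class size as a sensitivity figure, with the assumed CV.
- Claim a gain from baseline adjustment only if the assumed baseline prevalence and baseline-outcome association are written down with it.

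The cost is a short paragraph and a small table. Recruitment, design and analysis do not change.

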### Intervention program

#### Theoretical background and intervention contents

The intervention elements of the program will be based on the Social Cognitive Theory [18, 19]. This theory relies on the Social Learning Theory, as it was founded on principles of learning within the human social context [9], though it has also integrated several concepts from cognitive psychology. Key concepts of this theory, which will be addressed within the mobile phone-based program are (1) outcome expectations (i.e., beliefs about the likelihood and impact of the consequences of behavioural choices), (2) self-efficacy (i.e., beliefs about one’s personal ability to perform a desired behaviour which could be stimulated, for example, by mastery, experience or persuasion); (3) observational learning (i.e., learning new behaviours via exposure to them through interpersonal or media displays; e.g., through peer modelling); (4) facilitation (i.e., providing strategies, tools, and resources that make new behaviours easier to perform); and (5) self-regulation (i.e., controlling oneself via monitoring, goal-setting, feedback, and self-instruction).

The contents of the mobile phone-based program will rely on proven and widely-disseminated life-skills programs, like IPSY [11], ALERT [12] and Life Skills Training [13]. The program addresses (1) self-management skills, (2) social skills, and (3) substance use resistance skills. The program will be structured according to these major contents with the individually tailored web-based feedback and the mobile phone text messages in weeks 1–9 focusing on self-management skills, the messages in weeks 10–15 focusing on social skills, and the messages in weeks 16–20 focusing on substance use resistance skills. Boosters for each of the components will be provided in weeks 22–24.

#### Technological background

The intervention program will be developed using the MobileCoach system. Technical details of the system are described elsewhere [34, 35]. The MobileCoach system is available as an open source project on http://www.mobile-coach.eu. Password protection and Secure Sockets Layer (SSL) encoding are used to ensure the privacy and safety of data transfer.

#### Individually tailored feedback

The individual tailored web-based feedback will be given to study participants of the intervention group immediately after completion of the online baseline assessment within the school classes. This feedback comprises 4–5 screens, including textual and graphical feedback on stress in general, the individual level of stress in various domains compared to an age- and gender-specific reference group, and individual applied and suggested coping strategies. The feedback will use individual data gathered at the baseline assessment on perceived stress in different domains (school, leisure time, friends, family, and social media) and on individual strategies for coping with stress. Instruments for the assessment of stress and coping strategies will be derived from the study Juvenir 4.0, a national survey on stress in adolescents with more than 1500 participants [36]. Data of this survey will also be used to provide an age- and gender-specific feedback on the individual stress level.

#### Text messages

For a period of 6 months, program participants will receive between two and four individualized text messages per week on their mobile phone. These messages will be generated and sent by the fully-automated system. Within the first 9 weeks, the messages will focus on self-management skills; e.g., coping with stress, emotional self-regulation or management of feelings of anger and frustration. In weeks 10–15, the messages will focus on social skills; e.g., making requests, refusing unreasonable requests, meeting new people. In weeks 16–20, the text messages will focus on substance use resistance skills; e.g., recognizing and resisting media influences, social norms of substance use or the associations of self-management skills and social skills with substance use. Boosters for each of the components will be provided in weeks 22–24. The messages will be tailored according to the individual data from the baseline assessment and on text messaging assessments during program runtime; e.g., on substance use or the individual’s emotional state.

To exploit the full potential of current mobile phones, several interactive features, like quiz questions, tasks to create individually-tailored if-then behaviour plans based on implementation intentions, and message contests, will be implemented within the program. Due to the wide dissemination of smartphones in adolescents [20], several messages will also include hyperlinks to audio files (e.g., audio testimonials, motivational podcasts), as well as to thematically-appropriate video clips, pictures and related websites.

Table 1 shows a selection of the planned intervention elements, which are based on concepts derived from social cognitive theory [18, 19] and the major contents of widely-disseminated life-skills programs [11–13]: self-management skills, social skills, and substance use resistance skills.

**Table 1 Tab1:** Exemplary intervention elements of the mobile phone-based life-skills training

Concept derived from social cognitive theory	Content category		
	Self-management skills	Social skills	Substance use resistance skills
Outcome expectations	Individually tailored information on pros of using self-management skills to cope with stress.	Tailored information on the pros of applying social skills, e.g., making requests.	Information on pros of resisting alcohol, including social norms within an age- and gender-specific reference group.
Self-efficacy	Videos demonstrating easily applicable strategies to cope with negative emotions.	Contest on creating a bubble text on refusing an unreasonable request within a given situation presented on a picture.	Creation of if-then-plan for resisting invitation for smoking marijuana
Observational learning	Interactive message contest on stress regulation strategies.	Video showing exemplary behaviour on individually poorly developed social skills.	Video podcast showing peer models who successfully refused cigarette smoking.
Facilitation	Creation of if-then-plans for coping with the currently most severely affecting stress situation.	Podcasts introducing conversational skills or strategies for making requests.	Contest on creating a bubble text on refusing an alcoholic drink at a party presented on a given picture.
Self-regulation	Monitoring of and feedback on individual emotions.	Monitoring of and feedback on progress of individual social skills.	Monitoring of and feedback on individual alcohol use.

#### Prize draw

To stimulate active program engagement, program use will be associated with a friendly competition, which will allow program users to collect credits for each interaction (e.g., answering monitoring text messages, participating in quizzes, creating messages or pictures within contests, accessing video links integrated in text messages). The more credits participants will collect, the higher their chances will be of winning one of several attractive prizes which will be part of a prize draw (10 prizes with the sum of 500 Swiss Francs) after program completion. Participants will be able to retrieve their number of credits compared to the number of credits of other program participants’ of their group (similar starting date) at any time from an individual profile page.

### Assessments and outcomes

At baseline, demographic variables (age, sex, migration background), data on mobile phone use as well as characteristics of the schools (location, type of school) and school classes (level, size, number of students present) will be assessed.

Baseline- and follow-up assessments will includeProblem drinking in the preceding 30 days, assessed by the short form of the Alcohol Use Disorders Identification Test, the AUDIT-C [37]. This test comprises 3 items on (1) frequency of alcohol consumption, (2) quantity of alcohol consumption, and (3) binge drinking. Pictures will be used to illustrate the quantity of a standard drink, which corresponded to 12–14 g of pure alcohol. Based on a validation study of a large German sample, a cut-off of ≥5 will be used [38].30-days point prevalence rate for smoking abstinence (“not having smoked a puff” within the past 30 days according to the criteria of the Society for Nicotine and Tobacco Research [39]).Quantity of cigarettes smoked in the preceding 30 days by assessing the number of smoking days and the typical number of cigarettes smoked per smoking day.Cannabis use in the preceding 30 days assessed by an item of the HBSC study [5] addressing the number of cannabis consumption days.Perceived stress assessed by a four-item version [40] of the Perceived Stress Scale [41]. This scale measures the degree to which students appraised situations as stressful over the preceding month.Interpersonal competences, assessed by the brief version of the Interpersonal Competence Questionnaire [42], addressing the following domains of social competence: (1) initiation of relationships, (2) negative assertion, (3) disclosure of personal information, (4) emotional support, and (5) conflict management.

The primary outcomes of the planned study are (1) prevalence of problem drinking in the preceding 30 days according to the AUDIT-C and (2) prevalence of cigarette smoking in the preceding 30 days (having smoked at least a puff according to the criteria of the Society for Nictotine and Tobacco Research [39]).

Secondary outcomes arePrevalence of cannabis use in the preceding 30 days (having used cannabis at least once)Quantity of alcohol use in the preceding 30 daysQuantity of cigarettes smoked in the previous 30 daysFrequency of cannabis use in the preceding 30 daysPerceived stressInterpersonal competences

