## Methods/design

### Design and hypotheses

A two-arm cluster-randomised controlled trial will be conducted to test the efficacy of the *SmartCoach*, a mobile phone-based life-skills training program to prevent substance use among secondary school students. The efficacy of the intervention will be tested in comparison to an assessment only control group. The study participants will be assessed at baseline and at 6- and 18-months follow-up (Fig. 1). Our main hypothesis is that the individually tailored intervention program with a duration of 6 months will be more effective than assessment only, to prevent the onset and escalation of problematic alcohol and tobacco use at 18-months follow-up.

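### One efficacy hypothesis rests on two primary outcomes, each sized at a full two-sided 5% with no joint rule: familywise error is 7.8–9.8% if either suffices, and power is 67–75% if both are needed

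*Protocol article*

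**What the plan says.** Under Assessments and outcomes: "The primary outcomes of the planned study are (1) prevalence of problem drinking in the preceding 30 days according to the AUDIT-C and (2"), where the second item is the prevalence of cigarette smoking in the preceding 30 days.

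Under Design and hypotheses there is a single main hypothesis, that the programme does better than assessment only "to prevent the onset and escalation of problematic alcohol and tobacco use at 18-months follow-up". It does not say whether success on one substance is enough or both are needed.

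Under Sample size calculation, "an OR of 0.60 was expected for the main outcome measures". Each outcome then gets its own calculation at 80% power:

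- Problem drinking: 370 per group from a 25% control rate (α = 5%, "2-sided) in order to detect this difference based on a calculation using G-Power").
- Smoking: 410 per group from a 22% control rate ("α = 5%, 2-sided) in order to detect this difference").

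The larger figure, times a design effect of 1.60, gives 656 per group and 1312 in total.

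The Data analyses section says that efficacy will be tested through study group, time and their interaction in mixed models. It names no significance level, testing order, alpha split or success rule.

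**The concern.** The sizing spends the full 5% twice on behalf of one hypothesis. Whichever way the two results are then combined into a statement about that hypothesis, one of the planning figures may fail. If either win is enough, the chance of at least one false positive exceeds 5%. If both wins are needed, 80% describes one outcome and not the hypothesis.

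The practical case is a split result, for example smoking significant and drinking not. The protocol cannot then say whether its main hypothesis was met, and a rule chosen after the data are seen would carry little weight. The Discussion ties wider dissemination to the programme proving effective, so the answer matters.

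**Working it through.** **Inputs, all from Sample size calculation:** OR 0.60; control rates 25% (drinking) and 22% (smoking); two-sided α 0.05; power 80%; 13 students per class; ICC 0.05. The correlation *r* between the two test statistics is not given, so I assume a range of 0 to 0.8. Complete 18-month data are assumed throughout.

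**1. Reproduce the plan's figures.** Intervention rate = 0.6·odds/(1 + 0.6·odds), where odds is the control odds.

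- Drinking: 0.2/1.2 = 16.7%.
- Smoking: 0.1692/1.1692 = 14.5%.

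With pooled variance and no continuity correction, n = [1.96·√(2p̄(1−p̄)) + 0.8416·√(p₁(1−p₁)+p₂(1−p₂))]² / (p₁−p₂)².

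- Drinking: (1.96×0.5743 + 0.8416×0.5713)²/0.0833² ≈ 372, stated 370.
- Smoking: (1.96×0.5461 + 0.8416×0.5435)²/0.0753² ≈ 413, stated 410.
- Design effect: 1 + 12×0.05 = 1.60; 410×1.60 = 656 per group; ×2 = 1312. Exact.

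So the stated sizes are those of two separate tests, each at an unsplit 5%.

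**2. Power of each outcome at the planned size.** Effective n = 656/1.60 = 410 per group.

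| Outcome | α = 5% | α = 2.5% |
|---|---|---|
| Drinking | 83.7% | 75.8% |
| Smoking | 79.8% | 70.9% |

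**3. Either outcome suffices.** With independent tests, familywise error = 1 − 0.95² = 9.75%. For correlated tests it is one minus the bivariate normal probability that both |Z| < 1.96.

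**4. Both required.** With independent tests, joint power = 0.837×0.798 = 66.8%. For correlated tests it comes from the bivariate normal with the 5% powers above as margins.

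**5. Holm at 656 per group.** An outcome is significant if its p is at most 2.5%, or if it is at most 5% and the other is at most 2.5%. With independent tests:

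- Smoking: 0.709 + (0.798 − 0.709)×0.758 ≈ 77.7%.
- Drinking: 0.758 + (0.837 − 0.758)×0.709 ≈ 81.4%.
- At least one: 1 − (1 − 0.758)(1 − 0.709) ≈ 93.0%.

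| r | Familywise error, either suffices | Joint power, both at 5% | Holm, smoking | Holm, drinking | Holm, at least one |
|---|---|---|---|---|---|
| 0 | 9.8% | 66.8% | 77.7% | 81.4% | 93.0% |
| 0.3 | 9.5% | 69.2% | 77.1% | 80.7% | 89.6% |
| 0.5 | 9.1% | 71.1% | 76.8% | 80.3% | 86.9% |
| 0.8 | 7.8% | 74.9% | 76.2% | 79.2% | 82.0% |

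Counting only false positives that favour the programme, the either-suffices error rises from 2.5% to 4.9% with independent tests and to 3.9% at r = 0.8.

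**The case against.** The strongest reply is that a multiplicity rule is ordinary analysis-plan content, that the plan is not shown, and that the 5% appears only as an input to a χ² sizing calculation while the real tests are mixed models. Part of this stands. The document does not state the level at which the final tests will be judged, and silence on a procedure would not be a finding by itself. What remains is what the protocol does fix: one hypothesis, two primary outcomes, and a sample size that gives 80% only when each outcome is taken alone at a full 5%. An unseen rule that required both outcomes, or split alpha equally, would contradict that 80%.

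A reader might also infer that the plan must fail one way or the other. The documents do not support that, because two further readings are open:

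- **Separate claims per substance.** Each test keeps 5%, and power is 83.7% and 79.8%. The separate calculations fit this reading. The single main hypothesis and the single efficacy question in Data analyses weigh against it without excluding it.
- **A fixed testing order at 5%.** This controls the familywise error without resizing. Smoking tested first keeps 79.8%, and drinking then has the joint power of 67–75%. No order is declared.

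Finally, a reader might infer that error control cuts power to 71% and 76%. Those are Bonferroni figures and should not be quoted for Holm, which recovers most of the difference.

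**Conclusion.** The concern holds, with moderate severity. The two sizing calculations do not by themselves support a single efficacy claim. If either win is accepted, the familywise error is 9.8% (independent tests) down to 7.8% (r = 0.8). If both are required, power is 67% to 75% against the stated 80%. "Nearly doubled" would be a fair description of the error only up to a correlation of about 0.5.

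These figures rest on the protocol's own rates, odds ratio and design effect, on complete month-18 data, on an assumed correlation range, and on the simple two-proportion approximation used for sizing. They do not show that the trial is too small or wrongly designed. Against the unadjusted 79.8% and 83.7%, Holm costs about 2–4 points for smoking and 2–5 for drinking.

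**What to change.** State before outcome data are seen that efficacy on the two month-18 primary outcomes is judged by the Holm procedure: the smaller p-value against 2.5% and, if that is significant, the other against 5%. In Sample size calculation, restate power under Holm at 656 per group as about 76–78% for smoking, 79–81% for drinking and 82–93% for at least one, and give the assumptions (complete data, correlation 0.8 to 0).

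If the sponsor means that both outcomes must succeed, say so, keep 5% for each, and state the joint power of about 67–75%.

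The cost is a sentence or two of wording and a slightly less favourable power statement. No participants, assessments or procedures change.
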